### Study sample and eligibility

Prior evaluations of new LRT have recruited people into treatment (exposed) and control groups based on distance from their homes to new rail stations [59–66]. There is debate on the degree to which LRT investments induce new transit ridership versus shifting existing users from bus to rail [57, 71–73]. The current study attempts to overcome this limitation by focusing recruitment on university staff who both live and work near the rail line. We are not recruiting students, given the longitudinal design, nor physicians/faculty, whose level of education and income would be higher than average and not generalizable to the broader population. Compared to faculty or students, UCSD staff live twice the average distance from campus, and roughly 50% live in areas accessed by transit [74]. To be eligible, participants must be 18 years of age or older, be a full or part-time employee at the UCSD La Jolla campus, have commuted to the La Jolla campus ≥ 2 days/wk prior to COVID-19 closures, have lived in the same location for at least 1 year with no plans to move, can walk without assistance, can read and write in English or Spanish, and spend most of their time in San Diego County. We aim to have equal distribution across distance to LRT groups (< 1 mile, 1–2 miles, > 2 miles), with 50% of the sample comprised by females, people of color, and low-income staff.

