### Sample size

The TROLLEY study will enroll 465 English or Spanish speaking staff from UCSD’s La Jolla campus. We estimated a sample size of 340 was needed, considering a baseline of 45.1 (SD: 4.6) minutes/week of moderate PA using NHANES (2005–06) adult accelerometer data. We used a meta-analysis by Hirsh et al. and a conservative expected change of 3.46 min/day (95%CI: 2.20, 4.72) in transit-related PA from Miller et al. that evaluated a similar intervention in Utah [62, 78]. We set a significance level of 0.05 and power levels of 95% and assumed a 20% attrition rate. However, to ensure sufficient power for planned moderator analyses and in case of higher attrition rates than planned, we will recruit a total sample of 465 participants, stratified by LRT exposure, income, and race/ethnicity.

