### Statistical approach

Summary statistics of individual-level demographics, census block attributes, and baseline values of all outcomes will be calculated for the full sample and compared between the LRT exposure groups. Variables that are not balanced across groups will be adjusted for in subsequent analyses. Daily minutes of MVPA are typically positively skewed and will be transformed as needed to better approximate normality. Longitudinal changes in outcomes across the 3 measurement time points will be assessed using multilevel mixed effects linear (for continuous outcomes) or multinomial or ordinal logistic (for categorical outcomes) regression models, with the measurement time point included as an independent variable and adjustment for individual or block group level covariates (i.e., demographic characteristics, walkability, etc.). Covariates will be selected using a priori-knowledge and Directed Acyclic Graphs. Each outcome will be modeled separately. As we will have multiple measurement days nested within participants, a random participant-level intercept will be included in all models (alternative approaches that consider such clustering based on generalized estimation equations (GEE) will be also tested as a sensitivity analysis). We will also test the extent of block group clustering for each outcome (without covariates) by including a random effect for the intercept at the block group level and estimating the intra-class correlation (ICC). A likelihood-ratio test will assess fit between the models with and without clustering and, if significant, a random effect for block group will be included. We will assess effect modification by LRT exposure and other variables on both additive and multiplicative scales (when focusing on binary, categorical or count outcomes) using traditional approaches (stratified analyses coupled with heterogeneity tests or by including an interaction term in our models) [112, 113].

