We will perform additional sensitivity analyses to maximize covariate balance between LRT groups, considering techniques like inverse probability of treatment weighting (IPTW). IPTW removes confounding by creating a pseudo population in which every participant has an equal probability of being in the LRT- exposed group (i.e., home < 1 mile from LRT stop), assuming no unmeasured confounding. We will first model participants’ probability (i.e. the propensity score (PS) of being in the LRT-exposed group) [114] using imbalanced baseline demographic and environmental characteristics [115–117]. We will then calculate a weight using the PS values that will be included in regression models. Estimates from weighted and unweighted models will be compared and will also implement stabilized and truncated weights. We will examine the extent of missing data and conduct sensitivity analyses to compare characteristics of participants with complete versus incomplete data. Multiple imputation methods will be applied, assuming missing-at-random patterns and using default multiple imputation models (“mice” in R), with *N* imputed data sets generated (*N* corresponding the average % of missingness).

Test–retest reliability of the transit and COVID-19 survey measures, with two weeks in between assessments, will be assessed using intraclass correlation coefficients (ICC) [118, 119]*.* Values above 0.75 will be considered good to excellent reliability.

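### The propensity weight is placed in random-intercept models, where it can understate the standard error of exposure-by-time contrasts and barely adjusts level contrasts; weighted GEE would be safer (sensitivity analysis only, minor)

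*Protocol article*

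**What the plan says.** All statements are in the protocol article, Statistical approach, unless another section is named.

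- Model class: "a random participant-level intercept will be included in all models". The models are linear for continuous outcomes and multinomial or ordinal logistic for categorical ones.
- GEE appears in a parenthesis as another way to handle clustering: "generalized estimation equations (GEE) will be also tested as a sensitivity analysis". It is not linked to the weights.
- Status of weighting: "We will perform additional sensitivity analyses to maximize covariate balance between LRT groups, considering techniques like inverse probability of treatment weighting (IPTW").
- Where the weight goes: "We will then calculate a weight using the PS values that will be included in regression models".
- Exposed group for the propensity score: "home < 1 mile from LRT stop".
- Use of the result: "Estimates from weighted and unweighted models will be compared and will also implement stabilized and truncated weights".

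The article does not say how the standard error of a weighted model is obtained, and it attaches no test or decision to the weighted results.

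**The concern.** Taken together, these statements put an inverse-probability weight into a random-intercept model. Standard linear mixed-model software reads an observation weight as inverse residual variance, so a participant with weight 4 counts as measured four times as precisely. A propensity weight carries no such information. It says only how many similar people that participant stands for.

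Two things can follow, and they fall on different contrasts.

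- **Change over time by exposure.** The weight acts in full on the estimate, but a model-based standard error ignores the variance that unequal weights add.
- **Difference in level by exposure.** The participant variance swamps the weight, so the intended rebalancing hardly happens.

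At stake is what the sensitivity analysis can show. It may overstate the precision of the contrast closest to the primary aim. For levels, it may show agreement with the unweighted model that is no evidence of freedom from confounding.

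**Working it through.** **The plan's own figure.** There is none to reproduce. The article gives no weight distribution, standard error or error rate for the weighted analysis.

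**Inputs from the article.** Sample size: "we will recruit a total sample of 465 participants" (Sample size). Allocation: "We aim to have equal distribution across distance to LRT groups" (Study sample and eligibility), so about 465/3 = 155 are exposed. There are three waves. Seven wear days are requested per wave, with re-wear if fewer than four are valid.

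**Assumed, because not given.** Five valid days per wave; participant intraclass correlation 0.4; CV of the stabilised weights about 0.27 or 0.58; variance of participant slopes 0 or 0.02; propensity score from logistic regression on three covariates.

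**Step 1: time contrast, by formula.** The random intercept drops out of within-person change, so the weight acts in full. With weights unrelated to the residuals, the true variance is proportional to Σw²/(Σw)², which is (1 + CV²)/n. The model-based variance is proportional to 1/n. Hence model SE / true SE ≈ 1/√(1 + CV²).

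- CV 0.27: 1/√1.073 = 0.97
- CV 0.58: 1/√1.336 = 0.87

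**Step 2: time contrast, by simulation.** 1,500 replicates per setting, no true effect, no slope variance, weight used as residual precision, two-sided 5% test:

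| Weights | CV about 0.27: SE ratio; rejection | CV 0.58: SE ratio; rejection |
|---|---|---|
| Unstabilised | about 0.88; 8.5–9.1% | 0.77–0.78; 11.7–12.9% |
| Stabilised | 0.94–0.95; 5.7–6.5% | 0.81–0.82; 10.2–11.1% |
| Truncated at 99% | 0.95–0.96; 5.3–6.6% | 0.87–0.88; 8.6–9.5% |

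The two columns of figures agree through 2[1 − Φ(1.96 × ratio)]: a ratio of 0.94 gives 6.5% and 0.81 gives 11.2%. A further simulation without slope variance, over CVs of about 0.14 to 0.65, gave ratios of 0.97 to 0.82 and rejection of 6% to 11%. The formula in step 1 understates the narrowing for stabilised weights (0.87 against 0.81–0.82 at CV 0.58), so it is only a rough guide.

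With slope variance 0.02, rejection was 12.7–19.1% (unstabilised), 9.3–16.9% (stabilised) and 8.6–13.5% (truncated). Part of this is not due to weighting: the unweighted random-intercept model already rejected 8.6–9.3% when slopes were unconfounded.

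Across all settings, a participant-level robust standard error on the same weighted fit gave 3.2–6.1%. Where slopes were confounded, weighting did remove the bias in the time contrast (0.041 to −0.002; 0.075 to 0.002). For this contrast the fault lies in the standard error, not in the estimate.

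**Step 3: level contrast, by formula.** A participant's information about level is 1/(τ² + σ²/(m·w)). With total variance 1, intraclass correlation 0.4 and m = 3 × 5 = 15 days, τ² = 0.4 and σ²/m = 0.6/15 = 0.04.

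- w = 1: 1/0.44 = 2.27
- w = 4: 1/(0.40 + 0.01) = 2.44

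A weight of 4 therefore acts like 2.44/2.27 = 1.07.

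**Step 4: level contrast, by simulation.** With only the level confounded, bias went from 0.168 unweighted to 0.157 weighted, so 0.011/0.168 = 7% was removed. In the stronger setting it went from 0.295 to 0.279, so 0.016/0.295 = 5% was removed. When slopes were confounded too, the weighted level estimate was further from the truth than the unweighted one (0.202 against 0.170; 0.352 against 0.297). Narrowing was almost absent here: model SE / empirical SE was 0.95–1.06.

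**The case against.** The strongest reply is that the article states no error. It does not call the weight a precision weight and does not say that standard errors will be model-based. A condensed article may leave the variance estimator to the analysis plan. Weighted multilevel software with sandwich variance exists. The multinomial and ordinal models have no free residual variance for a weight to divide. The analysis is optional, its estimates are only compared with the unweighted ones, and stabilised and truncated weights are already foreseen.

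Most of this stands and limits the point. A reader might infer that the plan fixes invalid standard errors, or that the study will report false-positive LRT effects. The text supports neither: no estimator is named, no test hangs on the weighted model, and the primary models are unweighted. A reader might also take the rejection rates of 17% to 19% as the cost of weighting, but those need slope variance that already inflates the unweighted model. The narrowing figures apply to continuous outcomes only.

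What does not fall away is the combination itself. The article says that all models carry the random intercept and that the weight enters the regression models, while GEE is a separate clustering check. Nor would a robust standard error alone answer the damping in step 4, because that is a property of the estimate.

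**Conclusion.** The point holds in a limited, conditional form, and its severity is minor. If the weight is handled as residual precision with model-based standard errors, weighted intervals for exposure by time are somewhat too narrow: about 6% to 11% rejection at a nominal 5% for stabilised weights without slope variance. The rate is near nominal when weights are mild and stabilised or truncated, and moderately higher if they are left unstabilised. For level contrasts, the random intercept damps the weight whatever standard error is used, so agreement between weighted and unweighted estimates is weak evidence against confounding.

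The sizes rest on the assumed weight variability, intraclass correlation, number of valid days and slope variance, none of which the article gives. The conclusion does not extend to the unweighted primary models.

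**What to change.** State that the inverse-probability-weighted analyses are run as weighted GEE, with participant as cluster, independence working correlation and robust variance. Alternatively, bootstrap participants around that same weighted model and re-estimate the propensity score in each resample. Do not add the weights to the random-intercept model. Under independence a weight of 4 counts as 4 for both level and change, and the standard error does not depend on reading the weight as precision.

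The cost is one sentence of wording, since GEE is already planned, and slightly wider weighted intervals. GEE also relies more than the mixed model on how dropout is handled, so the weighted analysis should be run on the multiply imputed data that the plan already foresees.

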### Study Aims

The primary aim is to evaluate change in device-measured total and moderate-to-vigorous PA (MVPA), travel mode, and VMT. We expect minutes of MVPA and the proportion of AT (bike, walk, transit) trips, as a share of total trips, will increase. We also expect vehicle trips and VMT will decrease over time in those who live closest to LRT stations, compared to those who have less access to LRT.

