### Data collection

Participants will complete a measurement visit after consenting to participation. Participants will be assessed 3 times during the 2 years they are enrolled in the study; once when first enrolled (2022), 1 year after enrollment (2023), and 2 years after enrollment (2024). All data collection will occur after the opening of the UCSD Blue Line Trolley. However, time 1 survey measures ask participants about commute, PA, and spending behaviors both at the time of assessment and, retrospectively, prior to the pandemic and the new LRT. The campus closure in March of 2020 due to COVID-19 provides a noteworthy reference point to aid recall. The UCSD Exercise and Physical Activity Resource Center (EPARC) distributes accelerometer and GPS devices and instructs participants how to wear the monitors. TROLLEY staff call participants during the wear week to ensure compliance. Links to the online surveys are emailed to participants, and participants receive a $50 gift card after completion of all assessments at each time point.

Study data are collected and managed using REDCap electronic data capture tools hosted at UC San Diego [79]. REDCap (Research Electronic Data Capture) is a secure, web-based application designed to support data capture for research studies, providing: 1) an intuitive interface for validated data entry; 2) audit trails for tracking data manipulation and export procedures; 3) automated export procedures for seamless data downloads to common statistical packages; and 4) procedures for importing data from external sources. Participants are assigned a study ID and all records are coded with the study ID rather than personal identifiers. All device data files will be kept on secure servers at the Social Sciences Computing Facility and data will only be accessible to investigators and project staff.

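### The default mice models omit the participant level and the exposure-by-time term of the planned analysis; if outcomes are imputed in long format, the LRT-by-time effect shrinks by about 10% at the planned 20% attrition

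*Protocol article*

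**What the plan says.** The Statistical approach section of the protocol article fixes three things about imputation: the method, the assumption and the number of data sets. On the first two: "Multiple imputation methods will be applied, assuming missing-at-random patterns and using default multiple imputation models", with mice in R as the software. The number of imputed data sets is defined as "corresponding the average % of missingness".

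The same section describes the analysis that imputed data would have to serve: "As we will have multiple measurement days nested within participants, a random participant-level intercept will be included in all models". A block-group intercept may be added. Modification by LRT exposure is to be assessed "using traditional approaches (stratified analyses coupled with heterogeneity tests or by including an interaction term in our models". Study Aims states a contrast in change by distance, against people with poorer access: "We also expect vehicle trips and VMT will decrease over time in those who live closest to LRT stations, compared to those who have less". The design has three waves ("Participants will be assessed 3 times during the 2 years they are enrolled in the study", under Data collection), and the Sample size section "assumed a 20% attrition rate".

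The article does not say whether data are imputed long (one row per day or wave) or wide (one row per participant). Nor does it say which variables are imputed, or whether imputed data feed the main analysis or a sensitivity analysis.

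**The concern.** An imputation model should contain at least the structure that the analysis model will estimate. The mice defaults for ordinary variables are single-level regressions with main effects. They have no participant effect, no block-group effect and no time-by-exposure term, and the article adds none.

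In a long file this has two consequences. An imputed year-2 value does not depend on the same person's earlier values, so within-person correlation is diluted. The distance groups also receive a common time trend, so any difference in change between them is pulled towards zero. The moderator analyses are then the ones weakened, and the sample was raised from 340 to 465 partly to support them.

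A long file is a plausible reading. The activity outcomes are minutes per day, with 7 wear days at each of 3 waves, and the mixed model uses days as rows. A wide file would need up to 7 × 3 = 21 columns per outcome, or prior aggregation to one value per wave.

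**Working it through.** The article gives no numerical result for imputation, so there is no planned figure to reproduce.

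**Inputs from the article:** 465 participants in three equal distance groups (465/3 = 155 each), 3 waves, 20% attrition, and an expected change of 3.46 min/day. **Assumptions not in the article:** half the dropout by wave 2 and all of it by wave 3, so 100%, 90% and 80% are observed; total SD 12 min/day; ICC 0.3, 0.5 or 0.7.

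**1. Effect by hand (long layout, main effects only).** The group coefficient in the imputation model is the average of the wave-specific group differences, weighted by the rows observed. Let the effect be 0 at wave 1, half at wave 2 and full (1) at wave 3:

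(1.0×0 + 0.9×0.5 + 0.8×1) / 2.7 = 1.25/2.7 = 0.463.

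The 20% imputed at wave 3 receive this difference instead of 1, so the wave 3 minus wave 1 contrast becomes 0.8×1 + 0.2×0.463 = 0.893. With no effect at wave 2, the pooled value is 0.8/2.7 = 0.296 and the contrast 0.859. With the full effect already at wave 2, they are 1.7/2.7 = 0.630 and 0.926. None of this depends on the SD.

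**2. Within-person correlation by hand.** If imputed values are unrelated to the person's own other values, each pairwise correlation is multiplied by the share of pairs with both values observed: 0.9 (waves 1–2), 0.8 (1–3) and 0.8 (2–3). The mean is 2.5/3 = 0.833, so an ICC of 0.50 becomes 0.833×0.50 = 0.42.

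**3. Simulation at 20% dropout.** Predictive mean matching (the mice default for continuous data), dropout depending on the baseline outcome, 10 imputations, 200 replicates:

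| ICC | Full-data estimate | Long (ratio) | Wide (ratio) | ICC after long | Power: completers / long / wide |
|---|---|---|---|---|---|
| 0.3 | 3.482 | 3.124 (0.90) | 3.447 (0.99) | 0.25 | 0.50 / 0.44 / 0.53 |
| 0.5 | 3.390 | 3.046 (0.90) | 3.403 (1.00) | 0.42 | 0.62 / 0.48 / 0.63 |
| 0.7 | 3.491 | 3.088 (0.88) | 3.415 (0.98) | 0.59 | 0.78 / 0.59 / 0.79 |

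The ratios are to the full-data estimate. A second simulation with a different design (normal imputation, dropout completely at random, ICC 0.6) kept 0.896 at 20%. At 30% dropout, an assumption beyond the plan, the long ratios were 2.743/3.326 = 0.82, 3.110/3.551 = 0.88 and 2.877/3.446 = 0.83. Over both dropout rates the wide ratios ran from 0.98 to 1.04.

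The power loss has two sources: the shrunken estimate and an overstated standard error (at ICC 0.5, a mean of 1.597 against an empirical 1.490). The Monte Carlo standard error of a power of 0.48 is √(0.48×0.52/200) = 0.035, and all methods were run on the same simulated data sets.

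**4. Number of imputations.** Averaging missingness over waves gives (0+10+20)/3 = 10, or (0+0+20)/3 ≈ 7 if all loss is at wave 3. It gives fewer if complete variables enter the average. Relative efficiency is 1/(1+FMI/m), where FMI is the fraction of missing information: m = 7 and FMI 0.2 give 0.97, m = 7 and FMI 0.3 give 0.96, m = 10 and FMI 0.3 give 0.97. To hold the coefficient of variation (CV) of the standard error at 5%, m = 1 + 0.5(FMI/0.05)², which is 9 at FMI 0.2 and 19 at FMI 0.3. With m = 10 and FMI 0.3 that CV is 0.3/√18 = 7%.

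**The case against.** The strongest reply is that the defaults attach to variable types, not to a file layout. In a wide file, earlier waves are predictors and a group main effect in each wave's model carries the group-by-time difference. The same default matching then shows no meaningful bias. This stands: a reader might infer that default mice necessarily breaks the within-person correlation, and the article does not support that, because it states no layout.

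Second, a reader might infer that imputed outcomes replace the available-data mixed model. The article does not say so. The imputation sentence closes a paragraph that opens with sensitivity analyses and follows the propensity-score text, while the main model can use all available waves. If only covariates are imputed, the harm is smaller. This also stands.

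Third, modification by distance appears under subgroup analyses, although Study Aims states the contrast for vehicle trips and VMT. Leaving out the interaction does not by itself bias the overall time trend, and stratified analyses are also allowed. It is therefore too strong to call the affected term the sole primary effect.

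Fourth, layout and predictor lists are often left to a fuller document. That would answer a complaint about missing detail. It does not answer this one: the article itself commits to default models and to a rule for N, and its day-level analysis makes the harmful route the easy one to take.

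**Conclusion.** The mismatch is real; its harm is conditional. The stated imputation model is single-level with main effects, while the stated analysis is multilevel with exposure modifying change. If outcomes are imputed long, the group-by-time effect loses about 10% at the planned attrition (88–90% kept in simulation; 86–93% by hand, depending on when the effect appears), and an ICC of 0.50 falls to about 0.42.

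In that setting imputation does worse than analysing completers in bias and power, though not in mean squared error at ICC 0.5: √(1.490² + 0.414²) = 1.55 against √(1.659² + 0.060²) = 1.66 for completers. A mixed model on all available waves was not simulated, but it uses the completers' data and more. The power figures rest on the assumed SD and ICC; the proportional shrinkage does not depend on the SD.

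The rule for the number of imputations is a minor weakness. It costs 3–4% in efficiency in the cases shown and mainly makes standard errors and p-values less stable. The point is worth correcting before analysis; it does not invalidate the design.

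**What to change.** Replace the commitment to default models with wording to this effect:

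- Missing outcomes are handled by the mixed-model likelihood, using all available waves.
- Where imputation is used, for example for covariates or as a sensitivity analysis, name the imputed variables and the layout. Either impute wide (one row per participant, waves as columns, device days first summarised per wave, LRT group in each wave's model, and planned moderators as interactions or imputed within group), or use two-level models that include participant and time by LRT distance.
- Set the number of imputations to at least the percentage of participants with any missing value, with a floor such as 20. Under 20% attrition this gives at least 20 instead of about 7 to 10.

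The cost is analysis wording and computing time. Data collection and sample size do not change.
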